The CSIRO Total Wellbeing Diet (TWD), developed by the Commonwealth Scientific and Industrial Research Organisation (CSIRO) [17], is an energy-reduced, low fat, higher protein diet that meets the Australian nutrient reference values for daily intake [18], promotes a minimum thirty minutes of moderate physical activity per day, and has been extensively researched [9, 11, 19, 20]. In Book 2 of the TWD, the use of a pedometer is recommended to help individuals meet the suggested physical activity target [17]. Pal et al. have shown that setting a goal of 10,000 steps per day results in greater improvements to physical activity levels than the 30-min-a-day target [21]. This weight management program, along with the support of a dietitian, has been shown to cause significant improvements in cardiovascular disease risk biomarkers in overweight and obese individuals and weight loss of up to 10 kg after twelve weeks [11, 20]. However a mean weight loss of 5 kg has been reported by individuals following the TWD Book alone [22].

While weight loss can reduce the health risks associated with obesity [12, 23], many dieters have difficulty adhering to weight loss programs [24] or maintaining long-term weight loss [12, 23]. This can contribute to a sense of personal failure [6]. However, the lack of successful long-term weight loss in overweight and obese individuals may be due to the format of the weight management programs, such that dietary and lifestyle recommendations alone may not be enough [8]. In fact, the high attrition rate and/or weight regain after initial weight loss is so common that many researchers have tried to address this key issue by also adding other components to the treatment or intervention [22]. For example cognitive behavioural therapy, group support sessions, frequent medical or clinical appointments with health professionals and dietary supplements are additional strategies that have been included in some weight management programs or trials [4, 7, 25]. Research indicates that a multifactorial approach is likely to be optimal in achieving clinically meaningful weight loss results [22].

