### Assessments

All participants will be required to attend regular clinical appointments for a duration of approximately 15 min, as follows: at baseline, at weeks 6 and 12, and then again for a follow-up appointment at week 24. Prior to each appointment, participants will complete a Three-Day Food Record and selection of questionnaires to monitor compliance and address some of the secondary outcome measures. The Bouchard Three-Day Physical Activity Record [44] will be used to measure of total physical activity. The Three-Factor Eating Questionnaire (TFEQ) [45] will provide a measure of dietary restraint, disinhibition and hunger, and will also be used here to assess changes in satiety. The Self-Efficacy Scale [46] will be used to assess changes to participants’ self-efficacy. The WHO Quality of Life Questionnaire [47] will be used to determine changes in participants’ quality of life. The short version of the Depression Anxiety Stress Scale (DASS 21) [48] will be used to measure changes in general psychological wellbeing. The Self-Control (Brief) Scale [49] will be used to provide an understanding of participants’ impulse control as it relates to eating behaviour. The Diet and Physical Activity Survey, constructed using the Theory of Planned Behaviour [50], will be used to determine participants’ intentions with regard to the dietary and physical activity guidelines being used in the trial. The Survey of Weight Management Program has some general questions regarding the ease of use of the dietary and physical activity guidelines being utilized; there will be an extra section for Facebook Group participants to assess the preferred device for accessing the weight management information provided on Facebook. For Facebook Group participants only, the Social Media Survey will be used to assess participants’ attitudes to social media. The final questionnaire will also be administered to Facebook Group participants only; the Facebook Intensity and Network Density Scales contains a combination of questions used in previous social media research [51, 52]. It will be adapted for this study to assess the degree to which participants make use of Facebook, as well as the strength and frequency of the social interactions within the Facebook Group. In addition, the Facebook Group page will be printed at the end of each week to corroborate self-reported Facebook usage data and monitor participants’ online behaviour. Participants will be given questionnaires (including the Food Record and Physical Activity Record) at each clinic appointment, according to their group allocation. [For further information regarding the assessments please see Table 1: Schedule of Assessments.] Participants will be instructed to use their participant identification number only when completing all documents relating to this trial [42].

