### Statistical analysis

Based on a three group study with repeated measures, a sample size of 96 achieves 80 % statistical power to detect a medium to large effect size (Cohen’s *d* = 0.4); that is, a difference of 6 kg between the two intervention groups, with alpha set at 0.05. To allow for an attrition rate of 20 %, a total of 120 participants will be recruited; i.e. 40 participants per group. Stratified randomisation will be used to ensure that each group is matched in age and gender. The results will be analysed using a mixed repeated measures analysis of variance (ANOVA) design. Data will be expressed as mean (±SEM) and assessed for normality to ensure that the assumptions of the analysis are met. If significant between groups effects are present, post hoc analysis will be conducted using the Least Significant Difference (LSD) method. Statistical significance will be considered at p < 0.05. All statistical analyses will be performed using SPSS 21.0 for Windows (SPSS Inc., Chicago, IL), and conducted using the participant identification number only [42].

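### The named repeated measures ANOVA, as ordinarily run, drops anyone missing an included visit, which can bias the arm comparison in either direction and wastes observed data

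*Protocol article*

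**What the plan says.** The Statistical analysis section of the protocol article specifies: "The results will be analysed using a mixed repeated measures analysis of variance (ANOVA) design". On software it says: "All statistical analyses will be performed using SPSS 21.0 for Windows". It does not name the SPSS procedure or say which visits enter the model.

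The same section says that "a sample size of 96 achieves 80 % statistical power to detect a medium to large effect size", expressed as "a difference of 6 kg between the two intervention groups, with alpha set at 0.05". Attrition appears in the section once: "To allow for an attrition rate of 20 %, a total of 120 participants will be recruited; i.e. 40 participants per group".

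The Assessments section places the clinic visits "at baseline, at weeks 6 and 12, and then again for a follow-up appointment at week 24". Table 1 schedules weight, waist circumference and body composition, the three primary outcomes, at all four of them.

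Two other places bear on the point. The Background observes that "the high attrition rate and/or weight regain after initial weight loss is so common" that other researchers have added components to treatment because of it. The Abstract gives the purpose of the trial as testing whether social media improves adherence to a weight management program.

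**The concern.** A mixed ANOVA in this sense is the classical between-within design: arm between participants, visit within participants. It needs a complete set of outcome values for each person. SPSS's repeated measures GLM procedure deletes listwise, so one missing value at an included visit removes that person from every time point. If all four visits enter one model, a participant seen at weeks 0, 6 and 12 who misses only week 24 also loses valid week-6 and week-12 weights, although the intervention itself ends at week 12.

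People who complete every visit are selected after randomisation. If the chance of completing depends on how well someone is doing, and does so differently by arm, the arms compared are no longer the arms that were randomised. This trial is exposed to that: its intervention acts on adherence, and its own Background treats attrition as a common problem. Even without bias, the method discards measurements already taken in a trial of 40 per arm.

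**Working it through.** **1. The plan's own figure.** Inputs from Statistical analysis: 96 needed, 20% attrition. 96 / (1 − 0.20) = 120, which matches. In reverse, 120 × 0.80 = 96 complete cases (32 per arm), so 120 − 96 = 24 randomised participants would be missing from a complete-case analysis.

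**2. Scattered missed visits.** The 24 assumes that 20% is the total share with any missing value. Suppose instead (assumption) that each of the three post-baseline visits is missed independently with probability p, and that all four visits enter the model. Complete cases = 120 × (1 − p)³:

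| p per visit | (1 − p)³ | Complete cases |
|---|---|---|
| 5% | 0.857 | about 103 |
| 10% | 0.729 | about 87 |
| 20% | 0.512 | about 61 |

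At 10% per visit, the number analysed is already below the 96 on which power was based.

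**3. Bias in the Facebook-pamphlet difference.** The article gives no SD of change, correlation between visits or dropout model, so these are assumed: SD of change 5 kg, visit correlation 0.7, a set dropout rate in each arm, and dropout more likely after poor week-6 loss (logistic slope 0.5 to 2 per SD). In a large-sample simulation the mean changes were −8 kg (Facebook) and −2 kg (pamphlet), the article's hypothesised losses used as arm means. A negative difference favours Facebook.

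| Slope | Dropout, Facebook / pamphlet | All randomised (kg) | Completers only (kg) | Completers minus all (kg) |
|---|---|---|---|---|
| 1.0 | 20% / 20% | −5.99 | −5.99 | 0.00 |
| 0.5 | 10% / 30% | −6.02 | −5.69 | +0.33 |
| 1.0 | 10% / 30% | −5.99 | −5.42 | +0.57 |
| 2.0 | 10% / 30% | −5.98 | −5.17 | +0.81 |
| 0.5 | 30% / 10% | −6.01 | −6.35 | −0.34 |
| 1.0 | 30% / 10% | −6.00 | −6.56 | −0.56 |
| 2.0 | 30% / 10% | −6.00 | −6.79 | −0.79 |

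With equal dropout of the same pattern, the bias in the difference is about zero. With unequal dropout it is about 0.3 to 0.8 kg, and the arm that loses more people looks better than it should. If Facebook retains more people, as its rationale suggests, the completers' comparison understates its advantage.

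A likelihood-type estimate that also used the week-6 weights stayed within 0.02 kg of the all-randomised result. That is expected here, because dropout was made to depend on an observed weight.

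**The case against.** The strongest reply is that the article never says completers only. It names a design and a software package, and gives no procedure, analysis set or missing-data rule. Those are details that a condensed article may leave to a fuller plan. That plan could impute before the ANOVA, or carry out the mixed analysis as a linear mixed model. This stands as a limit on certainty: the loss of cases is inferred from how the named method is ordinarily run. It does not remove the point, which concerns the method the article does name. If a linear mixed model was intended, the wording needs correcting anyway.

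The week-24 consequence is also conditional. Hypotheses and Study design separate the 12-week intervention from the follow-up, and the 12-week comparison could be fitted without week 24. Lipids and insulin are measured only at weeks 0 and 12, so one four-visit model cannot serve every outcome.

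A reader might go further than the documents allow in three ways.

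- **That the inflation from 96 to 120 shows that completers will be analysed.** It does not. Inflating for attrition is routine whatever the analysis.
- **That at least 20% will be lost.** The 20% is a planning allowance, not a floor.
- **That the benefit is overstated by 25%, and by more if dropout differs by arm.** The 25% arises if 8 and 2 kg are completers' means and the 20% who leave each arm lose exactly 0 kg: 0.8 × 8 − 0.8 × 2 = 6.4 − 1.6 = 4.8 kg, and 6 / 4.8 = 1.25. The article says nothing about weight change in leavers and does not call 8 and 2 kg completers' means. Nor must unequal dropout enlarge the figure: at 10% Facebook and 30% pamphlet, 0.9 × 8 − 0.7 × 2 = 7.2 − 1.4 = 5.8 kg, and 6 / 5.8 is about 1.03. If those leavers had no post-baseline weights, a mixed model alone would not recover 4.8 kg either.

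**Conclusion.** The point holds as a risk of bias in either direction together with a loss of usable data. It does not show that the result will be overstated. The method named, as ordinarily run, would leave out about 24 of 120 participants at the planned attrition, and more if missed visits are scattered (about 87 complete cases at 10% per visit, assuming independence and four visits in the model).

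The bias in the Facebook-pamphlet difference is about zero with equal dropout of the same pattern. It is about 0.3 to 0.8 kg at 10% versus 30%, with its sign set by which arm loses more. Those sizes rest on the assumed SD, correlation and dropout model. They are modest against the planned 6 kg, but the better method is available at almost no cost, so the change should be made.

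**What to change.** Replace the ANOVA wording with a likelihood-based linear mixed model (SPSS MIXED) with group-by-visit terms, an unstructured covariance across visits and baseline weight as a covariate. Include all randomised participants with any post-baseline weight, in their allocated arm, and use every available visit. State the week-12 contrast explicitly, so that a missed week-24 visit cannot remove anyone from it. Treat waist circumference and body composition in the same way, each with its own baseline value.

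Add a sensitivity analysis for data not missing at random, for example with missing week-12 weight set to the baseline value. This is needed because the mixed model does not correct for leavers who return to baseline, and it also brings in participants with no post-baseline weight.

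The cost is a change of wording and slightly more analysis work. The planned software already includes the procedure, and no extra visits, measurements or participants are needed.

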### Hypotheses

In the present study, it is hypothesised that, compared to the Control Group, the Pamphlet Group will experience moderate improvements in outcome measures (including weight loss of approximately 2 kg) as a result of the twelve-week pamphlet-delivered intervention. It is also hypothesised that, compared to the Control Group, the Facebook Group will experience greater improvements in outcome measures (including weight loss of approximately 8 kg) as a result of the twelve-week social media-delivered intervention. It is further hypothesised that participants in the Facebook Group will experience greater improvements in outcome measures compared to the Pamphlet Group due to the support they receive from using Facebook. Finally, it is hypothesised that at the expiration of the twelve-week intervention period the Facebook Group will be self-sustaining with respect to their ongoing stable weight.

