### Outcome measures

The primary outcome measures for this study is weight loss, body composition and waist circumference. Secondary outcome measures include blood glucose, insulin and lipids, blood pressure, arterial stiffness and hip circumference, as indicators of changes to cardiometabolic disease risk factors. Dietary and physical activity compliance, eating behaviour, quality of life, mental well-being (stress, anxiety, and depression), self-control, self-efficacy, Facebook activity, and program evaluation will also be evaluated as further secondary outcome measures. These clinical and self-reported measurements have been chosen to test the participants’ adherence to the weight management program, and to compare the outcomes of the two different weight loss program delivery methods.

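### Pairwise arm comparisons depend on a loosely named between-groups effect which, read as the group main effect on weight, has low power at the plan's own figures

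*Protocol article*

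**What the plan says.** The Statistical analysis section of the protocol article names the model, "The results will be analysed using a mixed repeated measures analysis of variance (ANOVA) design", and then sets a decision rule: "If significant between groups effects are present, post hoc analysis will be conducted using the Least Significant Difference (LSD) method". The threshold is given as "Statistical significance will be considered at p < 0.05". The section names no group-by-time interaction, no time levels and no baseline adjustment.

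The same section powers the trial for one pairwise contrast: "a sample size of 96 achieves 80 % statistical power to detect a medium to large effect size", explained as "a difference of 6 kg between the two intervention groups, with alpha set at 0.05". The Hypotheses section expects losses of about 2 kg (Pamphlet) and 8 kg (Facebook) relative to Control, and predicts for the Facebook Group "greater improvements in outcome measures compared to the Pamphlet Group due to the support they receive from using Facebook".

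Participants attend "at baseline, at weeks 6 and 12, and then again for a follow-up appointment at week 24", and Table 1 schedules weight at all four visits. The response variable is described in different ways. Outcome measures has "The primary outcome measures for this study is weight loss, body composition and waist circumference", the Abstract speaks of change in weight, and Summary of intervention lists simply weight.

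**The concern.** In a mixed ANOVA the between-groups effect is ordinarily the group main effect, reported separately from time and from group-by-time. It compares arm means averaged over the repeated visits and judges them against variation between people.

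Body weight varies widely between people, and a treatment effect shows up as change within people. A test on averaged raw weight is therefore a weak way to detect it. If week 0 is one of the levels, randomisation makes the expected difference there zero, which shrinks the averaged effect further.

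The rule makes the Facebook–Pamphlet comparison conditional on this test. If the main effect was meant, the trial could fail to reach its central comparison even though the hypothesised losses are true and the data would show them under a baseline-adjusted analysis.

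**Working it through.** **Inputs from the protocol article**
- 96 evaluable participants, taken as 32 per arm; alpha 0.05 (Statistical analysis).
- 6 kg between the intervention groups, labelled d = 0.4, so implied SD = 6/0.4 = 15 kg.
- Effects relative to Control of 0, −2 and −8 kg; Facebook weight expected to stay stable after week 12 (Hypotheses).
- Weight at weeks 0, 6, 12 and 24 (Table 1).

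**Assumptions, not in the document**
- Within-person correlation ρ of 0.80 to 0.95, equal for all pairs of visits.
- Either half or all of the week-12 effect present at week 6, then held to week 24.

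**The plan's own figure.** 96/(1 − 0.20) = 120 reproduces. The 96 does not reproduce from d = 0.4. A plain two-group comparison needs 99 per arm, and 32 per arm gives about 36% power. No repeated-measures variant tried at the stated effect gave 96. The 15 kg SD is therefore only an implied value, and others are shown below.

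**Group main effect on weight, four visits.** With m visits and average effect fraction p̄:

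λ = n · p̄² · Σ(effect − mean)² / [SD² · (1 + (m − 1)ρ)/m], with 2 and 93 df.

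1. Mean effect = −10/3 = −3.33. Squared deviations: 11.11 + 1.78 + 21.78 = 34.67.
2. Half the effect at week 6: p̄ = (0 + 0.5 + 1 + 1)/4 = 0.625, so 6 kg becomes 3.75 kg. Full effect by week 6: p̄ = 0.75, so 6 kg becomes 4.5 kg.
3. At ρ = 0.90: variance = 225 × (1 + 2.7)/4 = 208.1; λ = 32 × 0.3906 × 34.67/208.1 = 2.08; power 23%.

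| SD | Half the effect at week 6 | Full effect by week 6 |
|---|---|---|
| 15 kg | 22–24% | 30–34% |
| 12 kg | 32–36% | 45–50% |
| 8.5 kg | 59–64% | 76–81% |

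Ranges are over ρ = 0.80 to 0.95. The 8.5 kg row is the SD if 0.4 were Cohen's f: √(34.67/3)/0.4 = 3.40/0.4. Power falls below 50% once SD exceeds about 9.4–10 kg (half at week 6) or 11.3–12 kg (full by week 6).

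Simulation of the SD 15 kg, half-at-week-6 case agrees: the condition was met in 22–25% of trials. It was met and the LSD Facebook–Pamphlet test was also significant in 12–14%.

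**What drives the loss** (SD 15 kg, half the effect at week 6)
- Weight at weeks 0, 6, 12 and 24: 22–24%.
- Weight at weeks 6, 12 and 24, without week 0: 36–40%.
- Weight at week 12 alone: 48%.
- Change from baseline at weeks 6, 12 and 24: 89–100%. At ρ = 0.90 the variance is 225 × 0.1 × (1 + 1/3) = 30, p̄ = 0.833, and λ = 32 × 0.694 × 34.67/30 = 25.7.
- Group-by-time interaction over four visits (6 df): 88–100%.

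**Baseline-adjusted Facebook–Pamphlet contrast at week 12.** Residual variance = 225(1 − ρ²). At ρ = 0.90 this is 42.75, SE = √(2 × 42.75/32) = 1.63 kg, and 6/1.63 = 3.67. Power is 75%, 85%, 95% and over 99% at ρ = 0.80, 0.85, 0.90 and 0.95.

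**The case against.** The strongest reply is that the damaging model is one reading among three.

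- **Change scores.** The Outcome measures section calls the outcome weight loss, and the Abstract calls it change in weight. If change is the response there is no baseline level and no dilution. Simulating the stated rule on change at weeks 6, 12 and 24 (SD 15 kg), the omnibus test plus LSD Facebook–Pamphlet succeeds in 0.835, 0.946 and 1.00 of trials at ρ = 0.85, 0.90 and 0.95. That is practically the same as the week-12 ANCOVA (0.841, 0.945 and 1.000).
- **Interaction.** The plural wording may be meant to cover group-by-time, which is well powered. An omnibus interaction can be significant through Facebook versus Control alone, but the LSD step then tests the pairs, so it does not block the contrast.
- **SD.** 15 kg is only implied, by a label that does not reproduce the sample size. At 8.5 kg the condition is met more often than not.
- **Omission.** An article may leave model terms and covariates to a fuller document.

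All four points stand as limits. A reader might infer that the plan definitely tests a four-visit main effect, that the trial would therefore usually miss its target, and that week 0 is the reason. The documents support none of these as fact. Neither the week-0 level nor raw weight as the response is stated, and raw weight without week 0 still has under 50% power at SD 15 kg.

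The objection does not remove the stated rule. The condition is printed in the article, so any later analysis plan must either follow it or depart from it.

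**Conclusion.** The point holds in limited form. The article fixes a decision rule without fixing which effect it tests. At SD 15 kg its power runs from about 22% to nearly 100% depending on the reading.

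On the most natural reading, power is about 22–34% at the plan's own figures, for a difference the plan says it has 80% power to detect. This rests on 32 per arm, the implied SD, the assumed correlations, the assumed week-6 pattern, and week 0 being a level of the model. A smaller SD weakens the point considerably. If change or the interaction was intended, the condition costs little and the defect is one of wording.

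**What to change.** Remove the condition on the group main effect. State the primary test as Facebook minus Pamphlet weight at week 12, adjusted for baseline weight, with a 95% confidence interval. Use either ANCOVA at week 12 or a linear mixed model for weeks 6, 12 and 24 with baseline weight as covariate and group-by-visit terms. Take Facebook versus Control and Pamphlet versus Control as secondary contrasts from the same model.

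If a change-score or interaction test was always intended, say so explicitly; that alone removes most of the problem. The cost is analysis wording only, because baseline weight and all follow-up weights are already scheduled.
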